## Abstract

**Background:**

US suicide rates have risen steadily in the past decade, and suicide risk is especially high in the months after discharge from inpatient psychiatric treatment. However, suicide research has lagged in examining *dynamic within-person processes* that contribute to risk over time among individuals known to be at high risk of suicide. Almost no research has examined how affective, cognitive, and physiological processes change over minutes, hours, or days to confer risk of suicidal behavior in daily life.

**Objective:**

This protocol describes a longitudinal study designed to examine real-world changes in risk of suicide across multiple assessment domains. Specifically, the study involves following adults known to be at high risk of suicide after discharge from inpatient psychiatric care using self-report, interview, actigraphy, and behavioral methods to identify proximal contributors to suicidal thoughts and behaviors. First, we hypothesize that negative affective experiences, which are featured in most major suicide theories, will comprise a latent factor indicative of psychache (emotional pain), which will predict increases in suicidal thinking over time. Second, we hypothesize that poor inhibitory control in the context of negative affective stimuli, as well as emotion-related impulsivity, will predict the transition from suicidal thinking to suicidal behavior over time. Third, we hypothesize that short sleep duration will precede within-person increases in suicidal ideation as well as increased odds of suicidal behavior among those reporting suicidal thoughts.

**Methods:**

The desired sample size is 130 adults with past-week suicidal thoughts or behaviors who are receiving inpatient psychiatric treatment. Participants will complete a battery of measures while on the inpatient unit to assess negative affective experiences, emotion-related impulsivity, inhibitory control, typical sleep patterns, and relevant covariates. After discharge from inpatient care, participants will complete 4 weeks of signal-contingent ecological momentary assessment surveys, as well as mobile behavioral measures of inhibitory control, while wearing an actigraphy device that will gather objective data on sleep. Participants will complete interviews regarding suicidal thoughts and behaviors at 4 and 8 weeks after discharge.

**Results:**

The study was funded by the National Institutes of Health in November 2020. Recruitment began in April 2021. Data analysis will begin after completion of data collection.

**Conclusions:**

This study will elucidate how affective, cognitive, and physiological risk factors contribute (or do not contribute) to within-person fluctuations in suicide risk in daily life, with important implications for extant theories of suicide. Of import, the examined risk factors are all modifiable; thus, the results will inform identification of key targets for just-in-time, flexible, personalized, digital interventions that can be used to decrease emotional distress and prevent suicide among those at highest risk.

**International Registered Report Identifier (IRRID):**

DERR1-10.2196/38582

## Introduction

### Background

US suicide rates have risen steadily in the past decade [1], particularly in rural areas [2,3]. Risk of death by suicide is especially high in the months after discharge from inpatient psychiatric treatment [4,5], particularly for people hospitalized because of suicidal thoughts and behaviors (STB) [6]. Despite this well-documented risk, research has made little progress in improving suicide prediction over the past 50 years [7]. Suicide research has been stymied by a focus on between-person factors that differentiate those who have and have not attempted (or died by) suicide, but many of these risk factors are relatively static, such as gender and race; research has lagged in examining dynamic, within-person processes that contribute to shifting risk over time among individuals who are already known to be at highest risk [8].

Leading *ideation to action* theories have enumerated negative affective experiences thought to contribute to suicidal ideation (SI), such as low connection [9], pain [9,10], hopelessness [9,11], thwarted belongingness [12], burdensomeness [12], defeat [13], and entrapment [13]. Negative affective experiences have been associated with between-person differences in current and past SI [9,12,13], and there is some evidence that within-person fluctuations in negative affective experiences may proximally predict SI [14-16]. Risk factors that are associated with the transition from SI to suicide attempts (SA) have been far less well studied [17]. More broadly, almost no work has examined our hypothesized cognitive, behavioral, and physiological risk factors of SA in daily life. We describe our protocol for a novel, transtheoretical, comprehensive examination of near-term risk factors for SI and SA among adults leaving psychiatric inpatient care, using multimodal ambulatory assessment of affective, cognitive, and physiological processes in an intensive longitudinal design.

### Negative Affective Experiences

Shneidman [10] argued that suicide is fundamentally rooted in unbearable psychache, “hurt, anguish, soreness, aching, psychological pain.” Psychological pain is robustly associated with suicide, whether because of psychiatric disorders [18], stressful life events [19], or physical pain or illness [20,21]. Nonetheless, modern suicide theories differ in the relative importance of negative affective experiences as they relate to suicide. For example, the Interpersonal-Psychological Theory [12,22] focuses on interpersonal facets of pain, namely perceived burdensomeness and thwarted belongingness [23]. The Three-Step Theory formulated by Klonsky [9] takes a broader view of pain as a prerequisite for SI, positing connectedness as a protective factor against severe SI in the context of pain. Both the Three-Step Theory and the hopelessness model described by Beck [11] emphasize hopelessness regarding the likelihood of negative affective experiences improving over time as a key predictor of SI. The Integrated Motivational-Volitional model described by O’Connor [13] argues that SI is prompted by feelings of defeat (consistent with the view expressed by Baumeister [24] of suicide as escape from aversive self-awareness) and entrapment.

Although these models indicate multiple nuanced facets of negative affective experiences, it is unclear whether people experiencing suicidality differentiate these facets and whether they have differential predictive power. Recent network analyses suggest that many of these negative affective experiences cluster together among individuals [25]. However, to date, these studies have not conducted analyses of how these negative affective experiences covary over time within individuals or how they differentially predict outcomes. We aim to test the coherence of negative affective experiences to determine whether these are, in fact, differentially related to SI or whether they are more accurately conceptualized as indicators of the broader construct of emotional pain (eg, psychache).

Although a plethora of cross-sectional studies have shown associations between these negative affective experiences and SI [26-33], little work is available on negative affective experiences as prospective predictors of SI. Longitudinal work has primarily examined negative affective experiences as predictors of SI over months or years [34,35] rather than as predictors of within-person short-term changes in SI. Recent ecological momentary assessment (EMA) research has demonstrated that many negative affective experiences fluctuate markedly at the within-person level, as does SI [15,36-40]; however, these studies have been limited by small sample sizes [15,36], short durations [37,38], and use of analog (community) samples [39-41]. Furthermore, negative affective experiences tell us little about which people with suicidal thoughts will go on to attempt, or die by, suicide, a central issue across ideation-to-action models.

### Emotion-Related Impulsivity

Research examining the broad domain of impulsivity in relation to STB has been mixed [41,42]. However, emotion-related impulsivity, the tendency to behave impulsively during high-arousal negative or positive affective states [43-46], shows clear associations with STB [47-55], nonsuicidal self-injury (NSSI) [56-60], and self-rated likelihood of future SA [51]. Furthermore, emotion-related impulsivity seems to amplify the association between other suicide risk factors, such as negative affective experiences, and SA [48]. Daily diary research further suggests that high emotion-related impulsivity is related to stronger within-person associations between negative affective experiences and NSSI urges [61], consistent with literature demonstrating that emotion-related impulsivity is characterized by problematic responses to negative affective experiences, rather than by greater affective intensity itself [44,45,62-66]. Emotion-related impulsivity is genetically driven and highly stable over time [67] and may thus serve as a trait-like marker of SA risk among those who experience SI.

### Cognitive Inhibition

Correlational research suggests that deficits in inhibitory control in the context of negative affective experiences are associated with SA and NSSI [47,60,62,68-70], especially among psychiatric populations [49]. Null effects for inhibitory control deficits related to SA have emerged when there was a lack of consideration of affective state [69-71]. That is, meta-analyses indicate that poor inhibitory control is tied to STB when people are tested while experiencing depressed mood or major depressive disorder or when negative stimuli are incorporated into the task [53,72]. This pattern of results highlights the need for integration of affective and cognitive domains jointly to consider STB risk [46,49,62,73].

### Sleep Disturbances

Sleep disturbances are associated cross-sectionally with SI and SA [74-77], and sleep problems predict later SA in adolescents [78]. Most of this work has used self-report omnibus measures of sleep [75], with limited ability to identify specific sleep domains as they relate to STB or to disentangle effects of objective and subjective sleep disturbances. To our knowledge, only 2 studies have examined prospective associations between actigraphy-assessed sleep and subsequent SI: Littlewood et al [79] found that short sleep duration predicted within-person changes in SI across days, and Bernert et al [80] found that variability in sleep duration predicted later SI above and beyond depression. No published work has examined objective sleep indices as predictors of SA in daily life.

However, there is strong evidence from neuroimaging [81] and behavioral research using naturalistic [82] and experimental [83] paradigms that sleep disturbances diminish inhibitory control [84-87] and that sleep problems are associated with other self-harm behaviors that can occur impulsively, such as NSSI [88]. Furthermore, prior work has shown that sleep disturbances contribute to impulsivity among patients diagnosed with psychiatric disorders [88]. Thus, based on the limited literature, we predict that reduced total sleep time (compared with an individual’s mean sleep duration) will affect likelihood of SA in the context of SI through decays in inhibitory control.

### Hypotheses

The goal of this study is to integrate examination of affective, cognitive, and physiological risk factors for short-term changes in suicidal thinking and suicidal behaviors among adults known to be at high risk within an ideation-to-action framework. To that end, our hypotheses are as follows:

Hypothesis 1a (H1a): within-person increases in affective suicide risk factors conceptually related to psychache (negative affective experiences) will individually precede within-person increases in SI.Hypothesis 1b (H1b): negative affective experiences will co-occur in daily life such that they are best conceptualized as indices of a single latent construct capturing emotional distress (psychache), which will itself predict short-term increases in SI.Hypothesis 2a (H2a): among those with SI, higher baseline self-reported emotion-related impulsivity will predict greater odds of SA over follow-up.Hypothesis 2b (H2b): among those with SI, poorer baseline behavioral indices of inhibitory control in the context of negative affective stimuli will predict greater odds of SA over follow-up. We also predict that, among those with current SI during EMA, lower EMA-assessed inhibitory control will prospectively predict subsequent SA.Hypothesis 3a (H3a): during the EMA protocol, short sleep duration will predict within-person increases in SI.Hypothesis 3b (H3b): during the EMA protocol, short sleep duration will predict greater risk of next-day SA among those with SI.Exploratory hypothesis 3c (H3c): the within-person effects of short sleep duration on SA will be mediated by within-person changes in inhibitory control assessed during EMA.

A visual depiction of these hypotheses is provided in Figure 1.

**Figure 1 figure1:**
[figure not shown]
Visual depiction of study hypotheses.

## Methods

### Project Overview

This is a single-group, repeated-measures (within-persons) observational study following adults with recent STB receiving inpatient psychiatric treatment (N=130). An ethnically diverse sample of participants will be recruited during inpatient psychiatric treatment in Lubbock, Texas, United States, based on past week STB. Eligible and interested participants will then complete the informed consent process, self-report surveys, clinical interviews, a computer task assessing cognitive inhibition, and a debriefing procedure. After discharge from inpatient care, participants will engage in a 4-week (28-day) EMA protocol that involves receipt of 7 signal-contingent self-report survey prompts per day between participants’ self-reported wake times and bedtimes. Participants will also be prompted to complete an abbreviated version of the cognitive inhibitory control task after each survey and asked to wear an actigraphy device for the 28-day follow-up period to assess objective indicators of sleep. Participants will be invited to complete a remote (phone or videoconference) follow-up interview assessing recent STB at 4 weeks and 8 weeks after discharge.

### Ethics Approval

All study procedures have been approved by the Texas Tech University Institutional Review Board (IRB2020-713; October 27, 2020). The study procedures were further approved by the first recruitment site (Covenant Health) on March 15, 2021. The study procedures, hypotheses, and all relevant documents were preregistered on the Open Science Framework on August 25, 2021 [89].

### Power Analyses and Sample Size Considerations

Given variability in EMA adherence, we conducted power analyses for 100 participants, while planning to recruit 130 participants to account for those with inadequate compliance. Most study aims will be tested using dynamic structural equation modeling, as described herein. In a recent Monte Carlo simulation study [90], adequate power (>0.80) for modeling of a single process (eg, SI) was demonstrated for moderate effects where n=100 with as few as 50 repeated measures (*t*=50). Thus, this study (*t*=196, 7 prompts per day for 28 days) is well powered even with a compliance rate as low as 57.1% (112/196; 4 prompts per day for 28 days) to examine within-person processes (H1a, H1b, and H2b). To provide more conservative estimates of power, a series of simulations with 100 replications were conducted for a random-effects (multilevel) logistic outcome using R software (The R Foundation for Statistical Computing) [91]. The assumptions for these simulations were as follows: (1) n=100, (2) within-person effects for all predictors, (3) standard normal distributions for all predictors, and (4) an intercept variance of 0.3. On the basis of these models, the study is well powered (>0.8) to detect standardized within-person effects as low as 0.1 with compliance as low as 64%.

For H2a, we used G*Power (Heinrich Heine University) [92] to conservatively determine the minimum detectable effect predicting any SA over follow-up with n=100, Cronbach α=.05, and β=.8, controlling for a moderate effect of SI on SA (0.3). We assumed an event proportion of 10% for the outcome based on recent literature [93]. On this basis, the study is powered to detect an odds ratio >2.63 for the effect of baseline emotion-related impulsivity or inhibitory control on follow-up SA risk. By way of comparison, recent research has demonstrated significant predictors of follow-up SA risk with odds ratios from 6 [94] to 13 [93].

For H3a and H3b, the models are identical to those for H1a, H1b, and H2B, except that analyses are conducted at the day level (*t*=28) to examine the effects of sleep. Previous studies have shown significant effects for the impact of sleep quality on next day SI (β=–.11) [79]. Although examination of within-day fluctuations in inhibitory control is exploratory (H3c), prior work showing large differences in inhibitory control between self-harm and control groups (Cohen *d*=0.84) [70] allowed us to conservatively estimate how day-level inhibitory control predicts SI and SA. Thus, we repeated our simulations outlined for H1a using *t*=28 and single predictors for sleep (H3a and H3b) and inhibitory control (H3c) in separate models. Models converged across repetitions, indicating that with n=100, the study is well powered (>0.8) to find standardized regression effects as low as 0.15 (representing small effects) for the within-person regressions of SI and SA on day-level inhibitory control or sleep disturbance.

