For H2a, we will estimate the effects of baseline emotion-related impulsivity and inhibitory control on odds of SA over follow-up, controlling for between-person differences in SI severity. To do this, person-mean estimates of SI and person-maximum estimates of SA (yes or no) will be calculated using EMA data. SA can then be predicted by baseline emotion-related impulsivity and inhibitory control scores using logistic regression analysis, controlling for participants’ SI severity. For H2b, we will then test whether within-person changes in state inhibitory control precede subsequent SA among individuals reporting SI. Using a 2-level random slope model, we will model time *t* inhibitory control (controlling for inhibitory control measured at time *t–*1) as a predictor of time *t*+1 SA, controlling for time *t* SI.

For sleep-related hypotheses, we will use 2-level random slope models, as described previously, but in which survey-level data on SI and SA have been pooled to create day-level variables (because sleep varies at the daily, but not survey, level). For H3a, we will use person-mean–centered total sleep time on day *d–*1 to predict next-day (day *d*) SI, controlling for day *d–*1 SI. Models for H3b will parallel those used to test H2a, whereby total sleep time on day *d*-1 will be used to predict next-day SA (day *d*), controlling for day *d* SI. For H3c, we will test whether the sleep-SA association (H3b) is mediated by within-person changes in inhibitory control. Building on the H3b model, we will add in the effect of sleep on day *d–*1 predicting inhibitory control on day *d*. To ensure that we are capturing sleep-related changes in inhibitory control, inhibitory control on day *d* will also be regressed on inhibitory control measured on day *d–*1. Finally, day *d* inhibitory control will be used to predict day *d* SA, controlling for day *d* SI. Indirect and direct effects will be calculated and tested for significance using the MPlus *model indirect* command.

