### Strengths and Limitations

As with all empirical research, this study includes several important limitations to consider. Several of these factors relate to the nature of the specific sample being recruited for the project. First, because of the nature of recruitment from an inpatient psychiatric treatment setting, the study sample is geographically restricted to adults from Lubbock, Texas, and the surrounding areas, and the results may differ from those obtained in larger metropolitan areas and in other parts of the United States, as well as internationally. Second, patients with manic or psychotic symptoms as well as those with cognitive impairment may be underrepresented in the sample, given the exclusion criteria related to the ability to provide informed consent to participate in the study. Third, the decision to base eligibility on recent STB will necessarily limit our ability to make inferences about postdischarge suicide risk among patients with no, or more distal, history of STB, who are at lessened, but nonzero, risk of postdischarge STB [4,5]. Fourth, although adequately powered, the desired sample size (N=130) will limit the ability to examine potential moderators of the study results across demographic and clinical characteristics (eg, race and ethnicity, sexual orientation, and mental health diagnoses).

Limitations also exist with respect to study methodology. Owing to concerns regarding the length and intensity of our baseline session, many study constructs will be assessed using self-report survey instruments, which can be subject to response biases and whose associations with each other may be attributable to shared method variance. Although several strategies have been implemented to improve completion rates of self-report, behavioral, and physiological data collection during the EMA protocol, we expect participants to vary in level of adherence to study procedures, which will also influence data quality and statistical power for planned analyses.

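### Power above 0.8 is stated for within-person effects on suicide attempts with no attempt rate given; at the document's only attempt rate, power is far lower

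*Protocol article*

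**What the plan says.** All power statements are in the protocol article, Power Analyses and Sample Size Considerations.

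- **Sample size used:** "we conducted power analyses for 100 participants, while planning to recruit 130 participants".
- **Prompt level:** the study is called well powered for H1a, H1b and H2b, citing a published simulation of one process, with SI as the example. H2b includes an SA model. The section then reports that "a series of simulations with 100 replications were conducted for a random-effects (multilevel) logistic outcome using R software", and concludes that "the study is well powered (>0.8) to detect standardized within-person effects as low as 0.1 with compliance as low as 64" percent. Four inputs are listed: n, within-person effects, standard normal predictors and an intercept variance of 0.3.
- **Day level (H3a–H3c):** the simulations are repeated with 28 occasions. Power above 0.8 is claimed in these words: "find standardized regression effects as low as 0.15 (representing small effects) for the within-person regressions of SI and SA on day-level inhibitory control". The claim extends to sleep disturbance. SA is named as an outcome here.
- **The only SA rate:** for H2a, "We assumed an event proportion of 10% for the outcome based on recent literature". It belongs to the "minimum detectable effect predicting any SA over follow-up with n=100". The Data Analysis Plan adds that for H2a "person-maximum estimates of SA (yes or no) will be calculated using EMA data".

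**The concern.** In a logistic model, power depends mainly on how often the outcome occurs. A simulation that lists no event rate cannot support a power figure for a rare outcome. SI and SA differ widely in frequency, yet one figure is stated for both. The cited single-process simulation, with SI as its example, does not address a rare binary outcome either.

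The transition from thought to attempt is the study's distinctive question. If H2b and H3b are described as well powered for small effects, a reader may take a credibility interval that includes 0 as a well-powered negative on sleep or inhibitory control. With about ten events such an interval is the likely result whether or not a small effect exists.

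**Working it through.** **Inputs from the article.** n = 100; 28 days or 196 prompts; 64% compliance; effects 0.15 (day) and 0.10 (prompt); standard normal predictors; intercept variance 0.3; 95% interval excluding 0, treated as a two-sided 5% test; 10% of persons with any SA (from H2a).

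**Formula.** For a log-odds slope b on a standard normal predictor, with N observations and event probability p, the information is about I = N·p·(1−p). Power = Φ(b√I − 1.96) + Φ(−b√I − 1.96).

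**1. Can the stated figure be reproduced?** Yes, but only for a frequent outcome. Day level, b = 0.15, N = 100 × 28 = 2,800:

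| Share of days with event | Formula | Simulated |
|---|---|---|
| 50% | 0.98 | 0.97 |
| 20% | 0.89 | 0.895 |
| 15% | 0.81 | – |
| 10% | 0.66 | 0.725 |

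The simulations fitted a random-intercept logistic model by maximum likelihood.

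**2. What does 0.8 require?** Required I = (1.96 + 0.842)²/b²: about 349 for 0.15 and 785 for 0.10. Solving N·p·(1−p) = I:
- Day level: p = 14.6%, about 408 SA-days of 2,800. With intercept variance 0.3, about 95% of participants would have an attempt within 28 days.
- Prompt level, N = 100 × 196 × 0.64 = 12,544: p = 6.7%, about 841 SA prompts.

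**3. What does 10% of persons give?** Setting the intercept so that 10% of persons have any event gives about 10.7 events in total. Power by number of events:

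| SA events | Day, 0.15 | Prompt, 0.10 |
|---|---|---|
| 10 | 7.6% | 6.2% |
| 20 | 10.3% | 7.3% |
| 50 | 18.3% | 10.9% |

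Simulated power at 10% of persons was 6.0% and 9.2% in two separate runs at day level, and 6.2% and 9.7% at prompt level. The last figure rests on 300 replications, with a Monte Carlo standard error of about 1.7 points.

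**4. Could repeated attempts by the same people rescue the claim?** Within-person information is greatest when a person has the event on half of all occasions (p(1−p) = 0.25). For 10 attempters:
- Day level: I = 10 × 28 × 0.25 = 70, power 24%.
- Prompt level: I = 10 × 196 × 0.25 = 490, power 60%; at 64% compliance I = 313.6, power 43%.

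**5. Other reading of the effect scale.** If the effect is standardized on the latent outcome scale, multiply it by √(π²/3 + 0.3) = 1.895. Then 0.15 becomes 0.284, and day-level power is 15% at 10 events and 24% at 20. The ceiling in step 4 also rises: at day level 0.284 × √70 = 2.38, so Φ(2.38 − 1.96) is about 66%, still below 0.8. At prompt level 0.10 becomes 0.189; 0.189 × √313.6 = 3.36, about 92%. That would require each attempter to report an attempt at half of all answered prompts.

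**6. Detectable effect.** Odds ratio = exp(2.802/√events): 2.4 per within-person SD at 10 events and 1.9 at 20, against exp(0.15) = 1.16 as stated.

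**7. Check on the 10%.** For H2a, exp(2.802/√(100 × 0.1 × 0.9 × (1 − 0.3²))) = 2.66, close to the stated 2.63. The rate is used consistently there.

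**The case against.** - **The 10% is not an input to these simulations.** This stands. A reader might infer that the plan assumed 10% and then miscalculated; the text shows only that no rate is listed. A condensed article may omit one that sits in simulation code. But any rate that yields 0.8 at 0.15 as log-odds would mean nearly all participants attempting, against 10% for H2a from the same EMA data.
- **A single figure such as 6–9% is too precise.** This stands. Attempts per attempter are not stated, the meaning of standardized is not defined, and the EMA item asks about suicidal behavior, which may be broader than attempts. If more participants have an event, day-level power at 0.15 rises slowly: about 11% at 20% of persons, 15% at 30% and 25% at 50%.
- **H2b and the 0.1 figure.** The sentence with 0.1 names neither SA nor H2b; context alone links them. Only the day-level statement names SA explicitly.
- **H3c.** It is already labelled exploratory, and no power is claimed for its indirect effect, which was not calculated here.
- **Inference rule.** A reader might infer that the plan treats an interval including 0 as evidence of no effect. The Data Analysis Plan says only that an interval excluding 0 is evidence for one.
- **Method.** The planned models are Bayesian. The check uses maximum likelihood, in line with the article's own multilevel logistic simulation. Tolerance of zero-inflated data concerns fitting and adds no events.

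**Conclusion.** The concern holds for SA. Power above 0.8 at 0.15 is stated for day-level SA without a base rate, and H2b is called well powered on a basis that does not address a rare outcome. Assuming the H2a rate carries over, power is about 6–10% at the stated effects, about 7–18% with 20 to 50 events, and about 15–24% at day level on the latent scale with 10 to 20 events. With 10 attempters and log-odds effects, the ceiling is about 24% by day and 43–60% by prompt. On the latent scale the day-level ceiling is still below 0.8; only the prompt-level ceiling passes it, and only under an extreme attempt frequency.

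Missed reports and restriction to people with current SI are not modelled; both would lower power further. Nothing here disputes the claim for SI, where power above 0.8 is attainable if SI is frequent.

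**What to change.** 1. Re-run the SA simulations with a stated base rate: about 10% of participants with any SA, range 5–20%. State the scale on which effects are standardized.
2. Restrict the 0.1 and 0.15 power statements to SI.
3. For SA in H2b (EMA part), H3b and the path from inhibitory control to SA in H3c, report the detectable odds ratio instead: about 2.4 per within-person SD at 10 events and 1.9 at 20, to be replaced by the re-run results.
4. State that an interval including 0 in these SA models is not evidence against an effect.

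H3c needs no relabelling. More than 100 replications (Monte Carlo standard error √(0.8 × 0.2/100) = 0.04) and a fixed rather than random slope are optional.

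The cost is a simulation re-run, some wording and a less favourable stated power. No extra participants are needed.
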